# HEPBURN - investigating the efficacy and safety of nebulized heparin versus placebo in burn patients with inhalation trauma: study protocol for a multi-center randomized controlled trial

**DOI:** 10.1186/1745-6215-15-91

**Published:** 2014-03-25

**Keywords:** Inhalation trauma, Pulmonary coagulopathy, Nebulization, Heparin, Mechanical ventilation

## Abstract

**Background:**

Pulmonary coagulopathy is a hallmark of lung injury following inhalation trauma. Locally applied heparin attenuates lung injury in animal models of smoke inhalation. Whether local treatment with heparin benefits patients with inhalation trauma is uncertain. The present trial aims at comparing a strategy using frequent nebulizations of heparin with standard care in intubated and ventilated burn patients with bronchoscopically confirmed inhalation trauma.

**Methods:**

The Randomized Controlled Trial Investigating the Efficacy and Safety of Nebulized HEParin versus Placebo in BURN Patients with Inhalation Trauma (HEPBURN) is an international multi-center, double-blind, placebo-controlled, two-arm study. One hundred and sixteen intubated and ventilated burn patients with confirmed inhalation trauma are randomized to nebulizations of heparin (the nebulized heparin strategy) or nebulizations of normal saline (the control strategy) every four hours for 14 days or until extubation, whichever comes first. The primary endpoint is the number of ventilator-free days, defined as days alive and breathing without assistance during the first 28 days, if the period of unassisted breathing lasts for at least 24 consecutive hours.

**Discussion:**

As far as the authors know, HEPBURN is the first randomized, placebo-controlled trial, powered to investigate whether local treatment with heparin shortens duration of ventilation of intubated and ventilated burn patients with inhalation trauma.

**Trial registration:**

NCT01773083 (http://www.clinicaltrials.gov), registered on 16 January 2013.

Recruiting. Randomisation commenced on 1 January 2014.

## Background

Inhalation trauma adds to the morbidity and mortality of burn patients [1,2]. Indeed, up to one third of burn patients require hospitalization due to inhalation trauma and a substantial percentage of these patients develop respiratory insufficiency. Moreover, approximately one third of burn patients with inhalation trauma eventually die, markedly more than burn patients without pulmonary involvement.

The underlying pathophysiology of inhalation trauma is only partly understood. Injury is thought to be at least the result of heat exposure to the airway mucosa or inhalation of noxious particles or toxic gases [3]. Injury of airway mucosa could induce an inflammatory response resulting in vascular leakage and pulmonary edema [4]. Pulmonary cast-formation could certainly play a role, since one study of burn patients shows disturbed alveolar fibrin turnover [5], and several preclinical studies show obstructive airway casts after smoke inhalation [6-9].

At present, therapy for inhalation trauma is merely supportive [10]. Animal models of smoke injury [6,7,9] and clinical trials of burn patients with inhalation trauma suggest that local treatment with heparin has beneficial effects [11,12]. The objective of the present trial is to determine the clinical efficacy and safety of frequent nebulizations of heparin in burn patients with inhalation trauma. Furthermore, the present trial investigates local effects of heparin on pulmonary coagulation and inflammation.

## Methods

### Design

The ‘Randomized Controlled Trial Investigating the Efficacy and Safety of Nebulized HEParin versus Placebo in BURN Patients with Inhalation Trauma’ (HEPBURN) is an international multi-center, double-blind, placebo-controlled, two-arm study. The trial is conducted in accordance with the declaration of Helsinki [13]. The Institutional Review Board of the Academic Medical Center, Amsterdam, the Netherlands, approved the trial protocol. The trial is registered at http://www.clinicaltrials.gov (NCT01773083). Patients or their legal representative have to give written informed consent before any study-related procedure is performed.

### CONSORT diagram

The CONSORT [14] diagram of HEPBURN study is presented in Figure 1. Consecutive burn patients with suspected inhalation trauma are screened. Demographic data and data on the extent of injury are registered regardless of meeting enrollment criteria. If excluded from participation, the reason(s) for exclusion are registered. For screening of inhalation trauma, a clinical [15] and a bronchoscopic [16] scoring system are used (Table 1).

**Figure 1 F1:**
[figure not shown]
**CONSORT diagram of HEPBURN.** *Until successful liberation from mechanical ventilation or for the maximum duration of 14 days. **For the maximum duration of 28 days.

**Table 1 T1:** Clinical scoring and grading of inhalation trauma

A. Clinical scoring system [15]		
1	History of being trapped in a house or industrial fire in an enclosed space	
2	Production of carbonaceous sputum	
3	Peri-oral facial burns affecting nose, lips, mouth, or throat	
4	Altered level of consciousness at any time after the incident and including confusion	
5	Symptoms of respiratory distress, including a sense of suffocation, choking, breathlessness, and wheezing or discomfort affecting the eyes or throat, indicating irritation of the mucous membranes	
6	Signs of respiratory distress, including stertorous, labored breathing, and tachypnea or auscultatory abnormalities, including crepitations or rhonchi	
7	Hoarseness or loss of voice	
B. Severity of inhalation trauma [16]		
0	No injury	Absence of carbonaceous deposits, erythema, edema, bronchorrhea, or obstruction
1	Mild injury	Minor patchy areas of erythema or carbonaceous deposits in proximal or distal bronchi
2	Moderate injury	Moderate degree of erythema, carbonaceous deposits, bronchorrhea or bronchial obstruction
3	Severe injury	Severe inflammation with friability, copious carbonaceous deposits, bronchorrhea or obstruction
4	Massive injury	Evidence of mucosal sloughing, necrosis or endoluminal obliteration

A. Clinical scoring system [15]. One point is given for the presence of each clinical factor considered to be suggestive of smoke inhalation to a total of seven points; a score of greater than 2 is considered fulfilling the criteria for unequivocal smoke inhalation. B. Severity of inhalation trauma based on bronchoscopic findings.

### Setting

HEPBURN is performed in three centers specialized in care of burn patients in the Netherlands (Red Cross Hospital, Beverwijk; Martini Hospital, Groningen; Maasstad Hospital, Rotterdam) and three specialized centers in Belgium (University Hospital Gasthuisberg - Leuven; Ziekenhuis Netwerk Antwerpen (ZNA) - Hospital Network Antwerp; Ghent University Hospital, Ghent).

### Study population

Intubated and ventilated burn patients, > 18 years of age with bronchoscopically confirmed inhalation trauma are eligible for participation. Notably, intubated and ventilated patients without skin burns, but with bronchoscopically confirmed inhalation trauma, are also eligible for participation in HEPBURN.

Patients are excluded if they are not enrolled within the first 36 hours after trauma, if intubated and ventilated for longer than 24 hours prior to trial enrollment, and if unlikely to survive for more than 72 hours or have burns covering > 60% of total body surface area (TBSA). Patients are also excluded if the expected duration of intubation and ventilation is less than 24 hours. Other exclusion criteria are history of severe chronic obstructive pulmonary disease (COPD) with (non-invasive) ventilation or oxygen therapy at home or repeated systemic corticosteroid therapy for acute exacerbations, witnessed or bronchoscopically proven aspiration, any history of pulmonary hemorrhage in the past three months, any history of clinically important bleeding disorder, known allergy to heparin or heparin-induced thrombocytopenia, and pregnancy or breast feeding.

### Randomization, blinding and intervention

Randomization is performed using ALEA® software (TenALEA consortium, Amsterdam, the Netherlands) and uses random blocks. Prior to randomization, patients are stratified for burn center and TBSA < 20% versus TBSA ≥ 20%. Patients are identified by study ID-numbers (randomization numbers) that are linked to the assigned study medication (heparin or normal saline). The pharmacist at each study site has access to the confidential file containing the randomization scheme, which links ID-numbers to appropriate ampoules. Since heparin and placebo are packed identically, they are provided with a temporary additional label ‘*verum*’ in case of heparin, or ‘placebo’ in case of saline. Before dispensing the medication to the ward, this additional label will be removed by the pharmacy, after which the medication is blinded for the study team. Nebulized volumes are identical.

Patients are randomly assigned to nebulization of study medication consisting of unfractionated sodium heparin (Pfizer, Melbourne, Australia) or sodium chloride 0.9% (Pfizer, Melbourne, Australia), administered every four hours (that is six times per day). For this, the total volume of identically packed 5 mL ampoules containing 25,000 IU of unfractionated heparin or 0.9% NaCl, is nebulized using an AeronebPro system (Aerogen Inc, Sunnyvale, CA, USA), connected to the ventilator circuit closest to the patient, but always in between the patient and the heat and moist exchanger if used. To prevent potential damage from nebulized heparin to the expiratory valve of the ventilator, a filter is placed in the expiratory limb of the circuit. Each nebulization session lasts 15 minutes. Nebulization of study medication is continued until tracheal extubation or death, but for a maximum duration of 14 days.

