### Follow-up

On the day of ICU admission, demographic and baseline data, as well as data on disease severity and extent of burn injury are collected. Data collection includes: gender, age, height, weight, functional status (independent, partially dependent or totally dependent), cardiac status (heart failure, according to the New York Heart Association (NYHA) [17], acute coronary syndrome *or* persistent ventricular tachyarrhythmia), alcohol status (in the past two weeks: 0 to 2 drinks/day, or more than 2 drinks/day), smoking status (in the past three months: never, former, or current). Data collection on relevant medical history include: COPD for which inhalation therapy or oral steroids are used, respiratory infection in the last month (upper or lower), history of active cancer, weight of loss more than 10% in the last six months, history of diabetes mellitus, chronic kidney disease, liver failure (Child-Pugh classification) [18], acquired immunodeficiency syndrome and use of relevant medications (including oral anti-diabetics, antibiotics in the last three months, statins, and corticosteroids). Regarding extent of burn injury, collected data include TBSA, partial or full thickness burn, Belgian Outcome in Burn Injury Study Group Index [19] and the Abbreviated Burn Severity Index (16).

Data on standard of care and clinical outcome variables (described below) are collected on a daily basis for the maximum duration of 28 days, until first discharge from ICU or death (whichever comes first). Data on length of stay in ICU and - hospital, mortality in ICU and hospital, and re-admissions to ICU are assessed on days 28 and 90 (Table 2).

**Table 2 T2:** Time schedule of study procedures

	**Day of admission (day 1)**	**Every day**^ **b/c** ^	**Days 1, 3, 5, 7, 9, 11 and 13**^ **c** ^	**Day of hospital discharge**	**Day 28**	**Day 90**
Screening and randomization						
screening^a^	X					
demographic data	X					
inclusion criteria	X					
exclusion criteria	X					
informed consent	X					
randomization	X					
Before start study medication						
blood sampling	X					
non directed broncho-alveolar lavage sampling	X					
Clinical procedures						
chest X-ray		X				
nebulization of study medication^c,d^		X				
blood sampling^c^			X			
non-directed broncho-alveolar lavage sampling^c^			X			
Clinical data collection						
%TBSA	X					
SAPS II	X					
Karnofsky score	X					
ABSI	X					
SOFA score		X				
LIS/OI		X				
ventilatory settings		X				

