### Statistical analysis

Patient characteristics will be compared and described by appropriate statistics. Data will be analyzed on an intention-to-treat basis. Normally distributed variables will be expressed by their mean and standard deviation and non-normally distributed variables will be expressed by their medians and 95% confidence levels. Categorical variables will be expressed as N (%). To test for normality, a D’Agostino and Pearson omnibus test will be performed [33]. Differences between groups will be tested by Student’s *t*-test for normally distributed data and Mann–Whitney *U*-test for not normally distributed data. Categorical variables will be compared with the Chi-square test or Fisher’s exact tests or when appropriate as relative risks. The difference of the primary effect variables will be analyzed using the Mann–Whitney *U*-test. The rate of freedom from ventilation will be analyzed according to the Kaplan-Meier method [34] and the results will be compared with the log-rank test hazard ratio’s are reported with 95% confidence limits. To take into account the stratification factors, we will perform an adjusted analysis. TBSA levels are group level data that will be included as a second level covariate in a multilevel linear regression model to assess the adjusted effect of our randomized treatment. Also the treatment effect on coagulation markers is investigated. Because they are clustered within each patient (repeated measurements) we will also use a multilevel model to evaluate the influence of the cluster effect on the model fit, that is we will compare the model fit without a second level (the patient) with the model fit that includes the patient as a second level. When appropriate, statistical uncertainty will be expressed by the 95% confidence levels. Statistical significance is considered to be at a *P* of 0.05. Analysis will be performed with SPSS version 18.1 (SPSS Inc., Chicago, IL, USA).

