Studies in healthy volunteers demonstrate that approximately 8% of nebulized heparin reaches the lower respiratory tract, of which 40% remains present 24 hours after inhalation [59]. The dose of nebulized heparin (applied as a single dose) that results in measurable increases in plasma aPTT is 150,000 IU and the half-life of the inhaled heparin is estimated to be 28 hours [60]. Since the type of nebulizer could affect the percentage of dose reaching the lower respiratory tract, we use the same nebulizer type as in previous clinical trials of nebulized heparin in critically ill patients [29,61]. In this trial, both dosing and duration of local heparin therapy are different from the two retrospective clinical studies of nebulized heparin in burn patients [11,12]. We based the dose, frequency and duration of heparin nebulization on a previous trial of critically ill patients, in which heparin nebulization was safe and associated with an increase in the number of ventilator-free days [29].

A major concern regarding safety could be the occurrence of serious bleedings. It might be argued that, due to endothelial injury and the increased vascular permeability resulting from the inhalational injury, the systemic impact of nebulized heparin and the risk of pulmonary bleedings might be higher in burn patients with inhalation injury when compared to critically ill patients without inhalation injury. However, two preclinical studies of burn and smoke inhalation injury models reported that heparin nebulization did not affect the systemic clotting time [6,9]. To date, data on safety of local heparin treatment in burn patients with inhalation trauma are limited. HEPBURN stops if complications occur significantly more often in one arm.

We chose the number of ventilator-free days at day 28 as the primary endpoint of this trial, a clinically relevant outcome parameter in critically ill patients. The effect of heparin may vary depending on the severity of injury [6]. However, the sample size of this trial does not allow subgroup analyses, for example, the evaluation as to what extent the efficacy of heparin depends on the severity of burn injuries.

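### The bronchoscopic grade is scored at screening, but the adjusted analysis names only TBSA, so its gain in precision and its protection against chance imbalance in airway injury are not used

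*Protocol article*

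**What the plan says.** All references are to the protocol article.

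- **Grade known before randomisation.** The section on the CONSORT diagram says: "For screening of inhalation trauma, a clinical [15] and a bronchoscopic [16] scoring system are used (Table 1"). Part B of Table 1 runs from 0 (no injury) to 4, which is described as "Evidence of mucosal sloughing, necrosis or endoluminal obliteration".
- **No limit on grade.** Under Study population, ventilated adults "with bronchoscopically confirmed inhalation trauma are eligible for participation", with no lower or upper grade. The same section adds that "intubated and ventilated patients without skin burns, but with bronchoscopically confirmed inhalation trauma, are also eligible for participation in HEPBURN".
- **Strata.** Under Randomization, blinding and intervention: "Prior to randomization, patients are stratified for burn center and TBSA < 20% versus TBSA ≥ 20".
- **Analysis.** Under Statistical analysis, the primary endpoint is compared by an unadjusted Mann-Whitney test. A further analysis follows: "To take into account the stratification factors, we will perform an adjusted analysis". TBSA is the only covariate named for that multilevel linear model.
- **Baseline data.** Under Follow-up: "Regarding extent of burn injury, collected data include TBSA, partial or full thickness burn", together with two burn indices. The day-1 rows of Table 2 add SAPS II and Karnofsky. Neither place names the bronchoscopic grade.

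**The concern.** The trial treats airway injury and measures time off the ventilator. Severity of airway injury at entry is therefore a natural baseline predictor to consider, and it is already scored. The Statistical considerations section justifies stratifying on TBSA by its link with longer ventilation and by the wish to keep burn severity even between arms. The same reasoning extends to the injury being treated.

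TBSA does not do this job by proxy. A patient with no skin burn falls in the lower TBSA stratum whether the airway shows patchy erythema or obliteration.

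Two things are at stake. If grade predicts ventilator-free days, leaving it out of the adjusted model gives up precision. And if grade falls unevenly between the arms, nothing in the described analysis shows how much of the observed difference comes from that. An adjustment chosen after an imbalance has been seen would be less credible than one named in advance.

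**Working it through.** **1. The plan's own sample size.** The reference trial's SDs are 4.0 and 7.1 (Statistical considerations). Pooled SD = √((4.0² + 7.1²)/2) = 5.76. For a 3-day difference, two-sided α 0.05 (sidedness is not stated) and 80% power, n = 2 × (5.76 × (1.96 + 0.84)/3)² = 57.9 with unrounded inputs, so 58 per arm. The stated figure reproduces, with power 0.80. The standard error of the treatment difference is 5.76 × √(2/58) = 1.07 days.

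**2. Chance imbalance in grade.** The documents give neither the share of patients at grade 3-4 (p) nor the ventilator-free days that such a grade costs (d). Both are assumptions: p = 30-50%, d = 3-7 days. The ordinal grade is cut in two for simplicity. Allocation is treated as unstratified, which overstates the imbalance somewhat if grade is related to centre or TBSA.

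SE of the between-arm difference in proportions = √(2p(1−p)/58). A 1-in-20 imbalance is 1.96 × SE or more. Shift in the treatment difference = imbalance × d.

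| p | SE | 1.96 × SE | Shift, d = 3 | d = 5 | d = 7 |
|---|---|---|---|---|---|
| 0.3 | 0.085 | 0.167 | 0.50 | 0.83 | 1.17 |
| 0.4 | 0.091 | 0.178 | 0.53 | 0.89 | 1.25 |
| 0.5 | 0.093 | 0.182 | 0.55 | 0.91 | 1.27 |

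The shift is 0.50/3 = 17% to 1.27/3 = 42% of the target. A median imbalance (0.67 × SE, about 6 points) shifts the difference by only about 0.17-0.44 days, or 6-15% of the target.

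**3. Power given an adverse imbalance.** With p = 0.4 and SD 5.76, suppose the heparin arm has 15 points more grade 3-4. Power of an unadjusted comparison of means falls from 0.80 to 0.67 if d = 3 and to 0.56 if d = 5. An imbalance of 15 points or more in either direction has probability 0.107 at p = 0.4 (exact binomial).

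**4. Precision gained by adjustment.** The share of outcome variance explained is R² = p(1−p)d²/SD². At SD 5.76 it runs from 0.21 × 9/33.2 = 6% to 0.25 × 49/33.2 = 37%. At an assumed SD of 8 it runs from 3% to 19%. Adjustment replaces SD by SD × √(1−R²). With 58 per arm and SD 5.76:

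| R² | Power | n per arm for 80% |
|---|---|---|
| 0 | 0.80 | 58 |
| 0.05 | 0.82 | 56 |
| 0.10 | 0.84 | 53 |
| 0.20 | 0.88 | 47 |
| 0.30 | 0.92 | 41 |

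These powers belong to a linear model such as the planned adjusted analysis, not to the Mann-Whitney test.

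**5. Covariate or stratum.** Six centres × 2 TBSA levels = 12 strata, about 116/12 = 9.7 patients each. A two-level grade would make 24 strata (4.8 each), and four grades 48 (2.4 each). A covariate is the more practical route.

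**The case against.** - **Covariates belong in the analysis plan.** Extra covariates for a secondary analysis, and individual form fields, are often left to a document not shown here, and nothing in the article excludes them. This has weight. But the article does specify an adjusted model, its purpose and its named covariate, so the point concerns a stated choice and not mere silence.
- **The grade may already be recorded.** A reader might infer from the Follow-up list and Table 2 that it is not kept. The documents do not support that: the CONSORT section has data on extent of injury registered for every screened patient, in the paragraph that introduces the score. This objection stands, so recording is only something to confirm.
- **The Discussion does not call grade prognostic.** "The effect of heparin may vary depending on the severity of injury [6") is about effect modification. It cites a preclinical source, and the example that follows is burn severity. This stands: a main-effect covariate would not address that sentence, which is not used as support here. Equally, the Discussion's refusal of subgroup analyses on grounds of size does not bar a main-effect covariate.
- **Randomisation already covers chance imbalance.** It does. A reader might infer that the primary test is biased, or that imbalance could by itself imitate or hide the 3-day effect. Neither follows. Overall type I error is unaffected, and even the 1-in-20 shift stays below half the target.
- **Heterogeneity may be narrower than the scale suggests.** Grade 0 is not confirmed trauma, and the exclusions for short expected ventilation and for unlikely survival may trim both ends. This is fair; the share at grade 3-4 remains unknown.
- **The remedy leaves the primary test untouched.** This is correct, and it limits the benefit.

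**Conclusion.** The point holds as a worthwhile improvement to the adjusted analysis, not as an error that undermines the trial. A severity score for the treated injury exists before randomisation, spans mild to massive injury, and has no place in the adjusted model as described. TBSA cannot replace it.

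The cost is some precision, and a shift that would go uncorrected if grade were imbalanced: about 0.5-1.3 ventilator-free days for a 1-in-20 imbalance, and about 0.2-0.4 days for a median one. These sizes rest on the assumed share at grade 3-4 and the assumed penalty in days. No statement in the article establishes that grade predicts ventilator-free days; if it does not, the shift and the gain both vanish.

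**What to change.** - Report the screening bronchoscopic grade (Table 1, part B) by arm with the other baseline characteristics, and confirm that it is carried onto the case report form.
- Before unblinding, prespecify it as a patient-level ordinal covariate, alongside TBSA and centre, in the adjusted analysis of ventilator-free days.
- Leave eligibility, the randomisation strata and the primary Mann-Whitney test unchanged.

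The cost is one more model term and possibly one form field copying a score already made. No procedure or patient is added. The limitation is that any gain in precision or protection against imbalance reaches only the adjusted analysis.
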